#### Interventions

All participants in the intervention groups receive the intervention four times a week for six consecutive weeks. During these six weeks, participants in the control group receive regular care.

The first intervention group receives MSim. During a session, three short, real life movies of approximately four minutes are shown of multiple activities (e.g. motor riding, dancing or horse riding) and from various perspectives. Matching music and sounds are played and the platform moves synchronically with the movies. This way, the participant on the platform moves in a passive way and is stimulated multisensory by means of visual, auditory, tactile and proprioceptive stimuli.

During WBV, the platform vibrates with a 30 Hz frequency and an amplitude of 1–2 mm. In an earlier study it was shown that these vibrations can safely be applied in old adults [28]. The duration of the WBV sessions is set to four minutes. During the WBV session a stationary motorcycle with idling engine is shown on the screen and matching sounds are played.

For the MSim + WBV intervention, the former two forms of passive exercise are combined. During 12 min participants alternately receive MSim (4 min) and WBV (2 min).

All forms of passive exercise will be applied using two commercially available motion simulation devices (the balancer, Fig. 1a and the wheelchair pod, Fig. 1b). During the sessions, participants are asked to take place on either one of the platforms and focus on the television screen. Hands are placed on the sidebars of the balancer or the wheelchair. Preferably the participant is seated as upright as possible.

The types of movies,the movement intensity of the platform and vibration intensity are documented. After each session the participant will be asked how much he/she enjoyed the session. Scores can be given on a scale ranging from zero to ten, with zero meaning they did not enjoy the session at all and ten meaning that they really enjoyed the session. Also, in the MSim and MSim + WBV group, the participants are asked which movies of the session they liked the most. For the MSim and MSim + WBV group respectively a top 3 or top 2 is documented. In the first week, at least one movie of each activity will be shown to the participant. After the first week, if any preferences are known for a participant, movies shown in the remaining sessions are chosen based on these preferences.

### Outcome measures

#### QOL and ADLs

To assess QOL and ADLs a series of questionnaires are used.

The EQ-5D-5 L [29] is filled in by the primary formal caregiver. It consists of five 5-point Likert scale questions, and is used to measure health-related quality of life based on five different domains (mobility, self-care, usual activities, pain/discomfort, anxiety/depression). An index value can be computed using the Crosswalk Index Value Calculator [30] with the value set from the Netherlands; an index value closer to 1 resembles a better quality of life. This index value of the EQ-5D-5 L can also be used for cost effectiveness analyses.

The Qualidem [31] is also filled in by the primary formal caregiver. The questionnaire consists of 40 items on a 4-point Likert scale and is specifically developed to quantify QOL in institutionalized patients with dementia. The following subscales can be distinguished: care relationship, positive affect, negative affect, restless tense behavior, positive self-image, social relations, social isolation, feeling at home, having something to do and other. A sum score between 0 and 120 can be obtained, a higher score reflects a better quality of life.

The Older Persons and Informal Caregivers Survey Minimum DataSet (TOPICS-MDS) is a set of brief, standardized questionnaires filled in by the primary informal caregiver, if possible in consultation with the participant [32, 33]. Next to demographic characteristics, outcome measures are comorbidity, quality of life, mood, functional limitations, mental health, social functioning, care use and care burden. For QOL the TOPIC-MDS includes the EQ-3D-3 L and two questions adapted from the RAND-36 [34, 35]. For ADLs the TOPICS-MDS includes a modified version of the Katz Index and an additional indicator of mobility [36]. Respondents are asked if the participant requires assistance for six basic functions (e.g. dressing, eating and bathing), and seven instrumental functions (e.g. grooming and taking medication). Responses are rated on a binary scoring system (dependent = 1; independent = 0) and summated, with higher scores representing greater functional limitations [32].

An adapted version of the Barthel-Index [37] is filled in by the primary formal caregiver and is used to measure ADL functioning and mobility. The adapted version is an observation scale that consists of ten items on a 5-points Likert scale. Sum scores can range between 0 and 90, with higher scores representing greater ADL functioning and mobility.

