## Abstract

**Background:**

Dementia affects cognitive functioning, physical functioning, activities of daily living (ADLs), and quality of life (QOL). Pharmacological treatments to manage, cure or prevent dementia remain controversial. Therefore development of non-pharmacological approaches to prevent, or at least delay the onset and progression of dementia is urgently needed. Passive exercise is proposed to be such a non-pharmacological alternative. This study primarily aims to investigate the effects of three different forms of passive exercise on QOL and ADLs of institutionalized patients with dementia. The secondary aims are to assess the effects of three different forms of passive exercise on cognitive functioning and physical functioning of institutionalized patients with dementia as well as on care burden of both the primary formal and primary informal caregivers of these patients.

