### Statistics

For each group, descriptive statistics of the sample’s sociodemographic and clinical characteristics at baseline will be determined. Analyses of covariance (continuous, normally distributed data) or non-parametric alternatives (ordinal, non-normally distributed data) will be used to examine differences between groups at baseline.

Since all primary outcome measures and some of the secondary outcome measures result from questionnaires, they will be of ordinal level of measurement and probably have a skewed distribution. Therefore, non-parametric tests will be used to analyze the data from the questionnaires. Gain scores (post-test minus pretest and follow-up test minus pretest/posttest) will be calculated and the differences between the groups will be analyzed using Kruskall-Wallis tests followed by Bonferoni corrected Mann-Whitney tests for paired comparisons.

The outcome measures related to cognitive and physical function will be of continuous level. If the data satisfy the assumptions, analyses of covariance will be used with scores on cognitive tests at T1/T2 as dependent variables, pretest scores as covariates and group (experimental groups, control group) as between-subjects factor. If the data do not meet the assumptions repeated measures analyses of variance or non-parametric methods with gain scores will be considered. Post-hoc tests will be performed with Bonferoni corrections for multiple comparisons. The data will be analyzed both according to intention-to-treat method (irrespective of adherence to intervention) as per-protocol (for selection of participants with sufficient adherence).

Missing data of items within questionnaires are substituted as prescribed for the individual questionnaires. If no prescription is available, the maximum likelihood method is used to substitute the missing values. Based on the internal consistency of the questionnaires, the maximum number of substituted values will be determined (Cronbach’s alpha >.80, max 50% of the items can be substituted).

A *p*-value of < 0.05 will be used to assess statistical significance. For all tests power and effect size calculations will be performed. Effect sizes will be calculated with Cohen’s d to measure the magnitude of difference of gain score measurements between each experimental and control group. Values benchmarking small, medium and large effect sizes: d = .20, d = .50, d = .80 [48].

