## Discussion

MSim and WBV are new and promising interventions for patients not able to be or stay involved in physical exercise. MSim and WBV are currently implemented in a variety of health care settings. However, there is limited evidence, if at all, of the clinical and cost-effectiveness of these interventions. To the best of the authors knowledge, the current trial is the first to study the proposed three forms of passive exercise in institutionalized patients with dementia.

The targeted population is a major strength of the study. The current in- and exclusion criteria ensure that the interventions are applied to a wide variety of dementia patients, thereby enhancing the generalizability of the results. Furthermore, the variety of movies and the possibility to adjust the intensity of the movements and sounds used for MSim makes that MSim can be personalized to a great extent. Consequently high adherence rates are expected in the present study.

MSim is a complex multi component intervention. Outcomes are expected in a wide range of variables. Therefore, in addition to the primary outcome measures, several secondary outcome measures are included, which have the potential to capture possible effects. This is a great advantage of the study. However we are also aware that the multiple comparisons leading from this variety of outcome measures will lead to a lack of statistical power of these comparisons. Therefore such additional analyses will be considered exploratory.

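### At least five unranked QOL and ADL scores, each tested on up to three gain scores at p < 0.05, are all primary, so the chance of a false primary result is well above 5%

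*Protocol article*

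**What the plan says.** The abstract states the primary aim for two domains together: "This study primarily aims to investigate the effects of three different forms of passive exercise on QOL and ADLs of institutionalized patients with dementia". The section on QOL and ADLs opens with "To assess QOL and ADLs a series of questionnaires are used" and describes them one after another, with no order of importance:

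- QOL: the EQ-5D-5L index ("The EQ-5D-5 L [29] is filled in by the primary formal caregiver"), the Qualidem ("A sum score between 0 and 120 can be obtained, a higher score reflects a better quality of life") and the TOPICS-MDS items ("For QOL the TOPIC-MDS includes the EQ-3D-3 L and two questions adapted from the RAND-36").
- ADLs: the modified Katz Index within TOPICS-MDS, with a separate mobility indicator, and the adapted Barthel Index.

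The Statistics section treats this whole set as primary: "Since all primary outcome measures and some of the secondary outcome measures result from questionnaires", so non-parametric tests apply. Gain scores are formed from pretest to post-test, pretest to follow-up and post-test to follow-up, and "the differences between the groups will be analyzed using Kruskall-Wallis tests followed by Bonferoni corrected Mann-Whitney tests for paired comparisons". The threshold is 0.05 throughout. Intention-to-treat and per-protocol analyses are both planned, and neither is given priority.

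The Sample size calculation section calls additional analyses, in a passage on subgroups, exploratory. The Discussion does the same for analyses of outcomes added to the primary ones. It gives as the consequence of many outcomes that "multiple comparisons leading from this variety of outcome measures will lead to a lack of statistical power of these comparisons".

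**The concern.** Nothing in the text says which score, which time point or which analysis set decides the primary question, or whether one positive domain is enough. A significant result on any of about 15 tests (five scores by three gains) could be reported as an effect on the primary aim, and the count doubles if both analysis sets are used. The Bonferroni step does not help here, because it works only between arms within one score and one gain. The exploratory label does not help either, because it is attached to analyses beyond the primary outcomes.

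The Discussion mentions loss of power but not the raised false-positive rate, which is the main effect of testing many outcomes without correction. It also concedes that the caregivers who complete the questionnaires cannot be blinded. A positive primary claim will therefore be examined closely, and it should not also depend on which score happened to cross 0.05.

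**Working it through.** The plan gives no familywise error figure to reproduce, so the check counts the tests and computes the error they imply.

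**Inputs from the protocol article.** Four arms, 1:1:1:1 (Randomization). 49 per group with 15% drop-out (Sample size calculation): 49 × 0.85 = 41.65, so 42 evaluable per arm. Five main scores (QOL and ADLs). Up to three gain scores, Kruskal-Wallis at 0.05, then Bonferroni-corrected Mann-Whitney tests (Statistics). The two RAND-36 questions and the mobility indicator would make eight scores; the main figures leave them out.

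**Assumed, because the article does not give them.** Between-score correlation 0 to 0.7. Within-person correlation 0.7, equal between all visits; under that structure the shared person component cancels in a gain score, so this value does not affect the result.

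**Step 1, independent tests as a reference.** Familywise error = 1 − 0.95^m.

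- m = 5 (five scores, T1 only): 1 − 0.95^5 = 22.6%
- m = 10 (two gains): 1 − 0.95^10 = 40.1%
- m = 15 (three gains): 1 − 0.95^15 = 53.7%

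These overstate the risk, because the scores are correlated and the third gain is the difference of the other two.

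**Step 2, simulation with no true effect (4 × 42).** A single score on a single gain gives 5.1% at Kruskal-Wallis and 3.8% after Bonferroni over all six pairs, so the method is sound for one score. With five scores, the chance of at least one false result is:

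| Correlation between scores | Gains | Omnibus | Then any of 6 pairs | Then any of 3 pairs vs control |
|---|---|---|---|---|
| 0 | 1 | 23.7% | 17.3% | 14.2% |
| 0 | 3 | 48.6% | 38.5% | 31.9% |
| 0.3 | 1 | 20.0% | 15.3% | 12.0% |
| 0.3 | 3 | 46.6% | 37.5% | 31.3% |
| 0.5 | 1 | 17.2% | 12.8% | 11.1% |
| 0.5 | 3 | 42.2% | 33.5% | 28.5% |
| 0.7 | 1 | 16.3% | 12.4% | 10.1% |
| 0.7 | 3 | 35.0% | 27.2% | 21.8% |

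The last two columns correct for six and for three pairs respectively. Entries move by one or two points between runs. In round terms the omnibus risk is 15–24% at T1 and 35–48% over three gains, and after all-pairs Bonferroni it is 11–18% and 27–40%.

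**Step 3, the narrowest definition of a false success.** Counting only an intervention that appears better than regular care after all-pairs Bonferroni, the risk is about 4–6% at T1 and 9–14% over three gains. The one-directional nominal rate is 2.5%.

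**Step 4, the same calculation after the fix.** With one score per domain at one time point and 0.025 each, 1 − 0.975^2 = 4.94% if the two are independent. The simulation gives 4.4–5.1% at the omnibus step and about 3% after all-pairs Bonferroni.

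**The case against.** A condensed article may leave the allocation of alpha to an analysis plan that is not shown, and the absence of a cross-instrument rule would be weak evidence by itself. That stands as far as it goes. Here, however, the article itself calls the whole questionnaire set primary and fixes the tests and the threshold. A later document naming one score would have to change this text.

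The omnibus figures also overstate what would count as success, since the plan follows Kruskal-Wallis with corrected pairwise tests and only a benefit over regular care supports the aim. This is fair and is why Step 3 is given. At T1 alone the directional excess is modest. Change from T1 to T2 is a doubtful route to a claim about a six-week effect, though the plan does not exclude it. If both domains had to be positive, the three-gain risk would be about 9–12%, but the article does not require both.

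Two stronger readings are tempting and not supported. A reader might infer that a false primary success is likely. With five scores, none of the simulated settings passes 50%; that needs all eight scores and three gains. A reader might also infer that the Bonferroni step is too strict. The article does not say whether it covers six pairs or three, and the Discussion foresees comparing the interventions with each other. All-pairs Bonferroni is valid and lowers the false-positive risk.

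Finally, the Discussion's sentence on power can be read as describing the cost of correcting many comparisons. It is then incomplete rather than wrong.

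**Conclusion.** The point holds. The article designates several unranked scores and gain scores as primary and controls error only between arms within each one. Followed as written, the chance of at least one false primary result is roughly two to nine times the nominal 5%: about 11–18% at T1 alone after the strictest reading of the pairwise step, rising to 35–48% over three gains at the omnibus step. For a false benefit over regular care it is about 4–6% to 9–14%, against 2.5%.

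The sizes rest on assumed correlations, with the upper ends belonging to uncorrelated scores and the lower ends to a correlation of 0.7. They also rest on five scores and one analysis set; counting the extra TOPICS-MDS items or the per-protocol set can only add to them. The direction of the conclusion does not depend on these choices. It should be settled before results are seen, because a choice of score made afterwards cannot repair it.

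**What to change.** Before results are seen:

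1. Name one QOL score and one ADL score as primary. The Qualidem sum is a natural candidate, being described as developed for institutionalized patients with dementia; the adapted Barthel is one for ADLs.
2. Define both as change from T0 to T1 in the intention-to-treat set.
3. Test the two at 0.025 each, or by Holm at 0.05, and say whether one positive domain suffices for a claim.
4. Label the other QOL and ADL scores, the T2 gains and the per-protocol results as secondary or exploratory.
5. State in the Discussion that uncorrected testing of many outcomes raises the false-positive risk.

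The change is to wording and needs no new data. Some instruments lose primary status, and power per domain falls somewhat. As an illustration, the stated 49 per group can be reached at f = 0.22 with two measurements correlated 0.4, a value the article does not give: 41 completers, 41 / 0.85 = 48.2, so 49. At 0.025 the same set-up needs 48 completers, 48 / 0.85 = 56.5, so 57 per group. Staying at 49 gives about 72–73% power instead of about 81–82%. That effect size comes from cognition, so the figures are only a guide for QOL and ADLs. Holm softens the loss, because once one domain is significant at 0.025 the other is tested at 0.05.

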#### Cognitive functioning

To evaluate the effects of passive exercise on cognitive functioning a neuropsychological test battery that covers de subdomains global cognitive functioning, executive functioning and verbal memory is used.

Global cognitive functioning is measured using the Mini Mental State Examination (MMSE) [38].The MMSE is a brief 20 item questionnaire test that is used to screen for cognitive impairment. The items refer to orientation, attention, memory, recall, and processing verbal and written information. Scores on this test can range from 0 to 30, a higher score reflects a higher level of global cognitive function.

To measure attention the Deary-Liewald simple reaction time task (SRT) [39] is used. During the SRT participants have to press a key, as quickly as possible in response to a single stimulus. The stimulus consists of a black cross appearing in a white square. Five practice trials are given (the practice trial can be repeated up to a maximum of 3 times to make sure the participant fully understands the task), after which instructions are repeated. The official test consists of a minimum of 15 trials. The test stops if the participant has 15 correct responses, correct being a response within the time limits of 150–3000 ms. Means and standard deviations are measured for each participant. Also the number of correct and incorrect (premature and anticipated) responses is measured.

The Stroop test is used to measure attention and inhibition [40]. It consists of three subtasks, all performed as quickly and accurately as possible within 45 s. For the first subtask a card is used with names of 4 colors (‘blue’, ‘green’, ‘red’, ‘yellow’) printed on it in black ink. Participants have to name the right words in the right sequence (left-right, top-bottom), as fast as possible. For the second subtask a card with colored blocks (blue, green, red, and yellow) is used. Participants have to name the right color of the block in the right sequence, as fast as possible. During the third subtask a card with names of colors (‘blue’, ‘green’, ‘red’, ‘yellow’) printed in opposite colors (e.g. ‘red’ written in blue ink or ‘yellow’ written in green ink) is presented to the participant. The participant now has to name the ink of as many words as possible in the right sequence. The score for each subtask consists of the number and the accuracy (%) of correctly named words or colors, a higher number and percentage reflects better inhibition.

The digit span forward (DSf) and backward (DSb) tests are used to measure respectively verbal short term memory and working memory [41]. During the DSf series of verbally presented digits are asked to be repeated. While during the DSb series of verbally presented digits are asked to be repeated in reverse order. In both tests the number of digits increases by one digit every two trials. The test is stopped when the participants fails to correctly repeat two consecutive series. The score is the number of successful repeated series, with higher scores indicating a better performance.

The short version of the Trail Making Test part A (TMT A) is used to measure visuomotor speed and attention. Participants have to draw a line between encircled numbers in increasing order (1–14) [42]. The time to complete the task is recorded. Lower scores indicate a better performance.

To assess divergent thinking and language skills, both the phonemic fluency and semantic fluency tests are used. For the phonemic fluency test participants are asked to name words starting with a specific letter (‘D’, ‘A’ and ‘T’) [43]. For each letter they have one minute to name as many words as possible. It is not allowed to use (part of) a word multiple times (e.g. snow, snowmen, snowball), names or digits. The total number of correct words from all three trials counts as score. A higher score reflects better performance. For the semantic fluency participants are asked to name as many ‘professions’ in one minute. The outcome measure is the total number of professions, with a higher score indicating a better performance.

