### Sample size calculation

Sample size is calculated with Sample Power 3. Since there is no data available on MSim or any comparable intervention, the sample size is calculated with an effect size estimation based on results of pilot studies on the chronic effects of WBV on cognition. Two pilot studies used the Stroop test score to evaluate these effects and resulted in an effect size of f = 0.22 [unpublished observations]. Power analyses with this value and use of repeated measures ANOVA, alpha 5%, power 80% and expected drop-out of 15% results in a minimal sample size of 49 participants per group.

Some additional remarks are needed to explain this sample size calculation. Since pilot data for QOL and ADLs are not available, the sample size estimation is based on the secondary outcome measure cognition and not on the primary outcome measures quality of life and daily functioning. Moreover, we are fully aware of the fact that with the calculated sample size additional subgroup analyses lack power. Including these analyses in the sample size calculation would result in unrealistic high sample sizes which would be practically impossible to realize due to factors like available budget, duration of the study and available number of potential participants. Additional analyses will be performed but will be considered exploratory.

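### Higher scores on all three Stroop cards are read as better inhibition, though two cards involve no conflict and the third also reflects naming speed

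*Protocol article*

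**What the plan says.** Under Cognitive functioning, the protocol article describes a battery that "covers de subdomains global cognitive functioning, executive functioning and verbal memory is used", and gives the Stroop test two constructs, attention and inhibition. On timing: "It consists of three subtasks, all performed as quickly and accurately as possible within 45 s".

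The cards differ in content:

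- Card 1: "For the first subtask a card is used with names of 4 colors (‘blue’, ‘green’, ‘red’, ‘yellow’) printed on it in black ink".
- Card 2: "For the second subtask a card with colored blocks (blue, green, red, and yellow) is used".
- Card 3: colour names printed in a non-matching ink, where the participant names the ink.

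The scoring rule does not separate them: "The score for each subtask consists of the number and the accuracy (%) of correctly named words or colors, a higher number and percentage reflects better" (the construct named is inhibition).

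The Statistics section plans analyses of covariance on the cognitive test scores at T1 and T2, with pretest scores as covariates. If assumptions fail, repeated measures analysis of variance or non-parametric methods on gain scores will be considered. The Sample size calculation section also draws on this test: "Two pilot studies used the Stroop test score to evaluate these effects". It names no card or index.

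**The concern.** The interpretation is attached to each subtask, so it covers cards 1 and 2. On those cards the correct response is the obvious one, and doing more of them in 45 s shows faster reading or naming. Card 3 has the conflict, but its count is also limited by how fast the participant can name colours at all. The stated rule therefore equates three speed-dependent counts with inhibition.

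A general gain in speed or alertness is a realistic rival explanation here. The Background cites work in which video and music improved alertness, and it proposes diffuse activation of brain regions. The Discussion adds that there is no social control group. If an intervention arm simply became quicker, the stated reading would allow a claim about inhibition that the data do not support. Conversely, a change in speed could hide a real change in inhibition on the raw card 3 count.

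**Working it through.** The protocol gives no figure for this point, so there is nothing to reproduce. The check has two parts. All Stroop means, SDs and speed changes below are assumptions.

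**1. Which scores move under a pure speed gain?** Assume baseline counts of 60, 40 and 20 on cards 1, 2 and 3.

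| Scenario | Card 1 | Card 2 | Card 3 | Card 3 / card 2 | Card 3 − card 2 |
|---|---|---|---|---|---|
| Baseline | 60 | 40 | 20 | 0.50 | −20 |
| All counts up 10% | 66 | 44 | 22 | 0.50 | −22 |
| Each item takes 10% less time (counts ÷ 0.9) | 66.7 | 44.4 | 22.2 | 0.50 | −22.2 |
| Each item is 0.075 s quicker | 66.7 | 42.9 | 20.7 | 0.48 | −22.2 |

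In the last row, 0.075 s is 10% of the card 1 item time, 45/60 = 0.75 s. The counts are 45/(0.75 − 0.075), 45/(1.125 − 0.075) and 45/(2.25 − 0.075).

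- All three counts rise in every scenario, and the stated rule reads each rise as better inhibition.
- If accuracy is correct responses out of those attempted and the error rate is unchanged, the three percentages stay put. Three scores move, not six.
- Under a proportional gain the ratio stays at 0.50. The simple difference moves from −20 to −22 and would falsely suggest worse inhibition.
- Under a constant saving per item the ratio is not exactly invariant. It falls by about 3.4% (0.483/0.50), while raw card 3 rises by about 3.4% (20.7/20). The ratio then errs against finding an inhibition gain.

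**2. How large could the apparent effect be?** For a 10% rise in the card 3 count with inhibition unchanged, d = 0.10 × mean / SD. Assume a card 3 mean of 9 to 14 and an SD of 6 to 7:

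- Mean 9: 0.9/7 = 0.13 and 0.9/6 = 0.15.
- Mean 14: 1.4/7 = 0.20 and 1.4/6 = 0.23.

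The range is 0.13 to 0.23, around the protocol's benchmark of d = .20 for a small effect. It scales directly with the assumed mean-to-SD ratio.

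Taking 49 × 0.85 = 41.65, so about 41 completers per group, an unadjusted two-sided two-group t test at 5% has noncentrality d × √(41/2). That is 0.59 at d = 0.13 and 1.04 at d = 0.23. Such a difference would reach significance about 9% to 18% of the time.

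**Does the planned analysis remove the problem?** No. The pretest covariate adjusts for baseline differences in speed, not for a gain in speed after randomisation.

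**The case against.** Several points on the other side stand.

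- Accuracy is scored as well as number. If the rule is read as requiring both to rise, a pure speed gain would not meet it.
- The paragraph names attention alongside inhibition, and cards 1 and 2 can reasonably serve attention.
- The cards are scored separately, so a uniform rise would be visible. Simple reaction time and the Trail Making Test part A, the latter labelled visuomotor speed and attention, give further evidence on speed.
- Cognition is a secondary outcome, and the hypotheses concern cognitive functioning in general. Inhibition appears in the Background as an example from earlier vibration studies in other populations, not as a stated target of this trial.
- The size is assumed throughout. The planned Bonferroni correction would lower the significance rates above, and baseline adjustment would raise them by an unknown amount.

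A derived score might also be defined in an analysis plan that is not shown, and its absence from the article is not the fault. The fault is that the article does state an interpretation, and that interpretation does not fit cards 1 and 2. Nothing in the text says that the separate cards or the speed tests will be used to qualify it.

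**Conclusion.** The scoring sentence should be corrected. It reads higher values on any card as better inhibition, while two cards as described involve no conflict and the third mixes inhibition with speed. A speed gain could therefore be misread as an inhibition effect. For a 10% gain this would be about d = 0.13 to 0.23, given the assumed means and SDs. The consequence is limited to one test in a secondary domain.

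A reader might infer more than the documents support:

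- **That a false executive-function effect will be reported, on all six Stroop values.** The article does not say how number and accuracy are combined or what happens if they disagree. A pure speed gain moves at most the three counts.
- **That the sample size is undermined.** The pilot effect size came from a Stroop score, but the card or index is not named, so nothing follows about whether it measured speed or inhibition.

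**What to change.** - Reword the scoring sentence: cards 1 and 2 measure reading or naming speed and attention, and inhibition is inferred only from card 3 relative to card 2.
- Prespecify one inhibition index per visit: log(card 3 correct / card 2 correct), with a small constant, fixed in advance, added for zero counts. Analyse it by the planned ANCOVA with its own T0 value as covariate.
- Report raw card 3 count and accuracy as supportive scores.
- Do not use card 3 minus card 2, because it changes under a proportional speed gain.

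**Cost.** All counts are already collected, so this is a change of scoring and wording. The ratio is noisier than a raw count, and participants near zero on card 3 will contribute little information, which is a real limitation in institutionalised patients with dementia. Its protection is exact only for a proportional speed gain and before the constant is added. With an illustrative constant of 0.5, the move from 20/40 to 22/44 shifts the log ratio only from −0.681 to −0.682. Under a constant saving per item the index leans against finding an inhibition gain, so it should be read beside the three card counts.
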